### Controls

3.8

#### Description and delivery of TENS

3.8.1

Participants who are allocated to the control intervention group will receive TENS therapy. TENS is mainly used for musculoskeletal and neuropathic pain treatment and also offers functional benefits. The device sends electrical impulses through conductive rubber electrodes to the skin of the impaired region. TENS is used in medical settings and can be self-administered by patients at home. In TENS only the frequency modulation is possible. The applied frequencies range from 2 to 120 Hz. The pain region must be in the middle of the 2 electrodes, with a maximum distance of 20 cm. Eligible participants will be identified in the same way as the HTEMS group. Randomization determines allocation. TENS will be performed with a DoloBravo therapy device 10-05 (MTR GmbH, [name], CE 0123), which is operated by a small 9 V block battery. A medical engineer will provide use instruction. The first treatment is performed and supervised by a training therapist at the Institute of PMR. Frequency (intensity) is applied according to the manufacturers‘ instructions. The participant is educated for home-based therapy and the treatment should be used daily for 30 minutes for at least 5 days per week during the 8 weeks of intervention. Additionally, participants‘ compliance will be checked by reading out the toolbox.

### Baseline-examination

3.9

Shortly after consent is obtained, the study team will assess the following parameters and record all data in each patient's case report form (CRF):

age and sexheight and weightdiagnosis and co-morbiditieslevel of educationsmoking behaviorchemotherapy scheduleCIPN/grading

Participants are asked to fill out the questionnaires (QLQ-CIPN 20 and QLQ 30) in paper form. Clinical examination will be performed by physicians at the Institute of PMR.

### Follow-up, final examinations

3.10

Patients will be contacted by the study team after 1 week to identify any problems with the device. After 8 weeks of electrotherapy (HTEMS or TENS), the outcome assessments (physician-reported outcome and patient-reported outcome) from baseline will be repeated. Reporting of results will be in accordance with the principles of the Consolidated Standards of Reporting Trials (CONSORT) statement.^[19]^

### Process evaluation and compliance

3.11

Participants‘ compliance in the intervention and the control group will be checked by reading out the toolbox of the HTEMS and TENS device. The minutes in use and intensity will be recorded for every device. Furthermore, patients’ diaries will be evaluated to check for accordance with the toolbox records.

### Monitoring

3.12

A detailed monitoring and quality plan that complies with Good Clinical Practice guidelines will be developed. This monitoring and quality plan will involve standard operating procedures as well as documentation of any safety parameters related to electrotherapy. Additionally, this includes monitoring of the rate of recruitment, identifying and resolving data errors or omissions on the forms, monitoring for protocol violations, and looking for unanticipated events. Quality assurance includes checking of the case report forms for completeness and clarity, cross-checking with source documents, and clarification of administrative matters. Furthermore, the site monitors will assure that the study is conducted according to the protocol design and regulatory requirements. Complications and side effects will be documented. The number of patients who will not complete the full course of therapy and the reasons for this will be recorded. Since this is a pilot study and due to the sample size no interim analyses will be performed. The Institute of General Practice, Family Medicine, and Preventive Medicine is responsible for the monitoring and the monitor is independent from the sponsor and competing interests.

### Potential harms and patient safety

3.13

According to current literature, it is not to be expected that complications or harm will be caused by electrotherapy. The observed side effects of HTEMS were nervousness and sleep disorders.^[13,15]^ Nevertheless, we will monitor potential harms. Undesirable or adverse effects of electrotherapy will be registered by the study team. The study team reports the events in the CRF as soon as they become aware of the event. They are responsible to judge whether the adverse event is associated with the intervention. Stopping criteria comprise: dysesthesia, aggravation of symptoms, adverse events with the devices, incompatibility of the electrodes, progress of underlying disease, or any new upcoming exclusion criteria during the intervention. Additionally, after inclusion study participants get a telephone number of a study team member to report any adverse events or other concerns. There are no concomitant care and interventions that are prohibited—usual care will continue during the study period. Insurance for the study participants is provided. Study data will be locked and only the study team will have access. Included patients are anonymized with a study identification number.

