## Introduction

1

The use of chemotherapy has led to prolonged remission and survival in numerous cancer diseases. Chemotherapeutic agents have negative side effects and some of them are long-lasting. One of the most common adverse side effects of taxanes, platins, or vinca alkaloids is chemotherapy-induced peripheral neuropathy (CIPN). Prevalence of CIPN was reported in 30% to 40% of patients treated with neurotoxic chemotherapy and may be transient or permanent.^[1,2]^ CIPN appears predominantly as sensory neuropathy and affects the peripheral parts of the extremities in a “stocking and glove” distribution. It often presents with symptoms like paresthesia and numbness or tingling, but pain and motor symptoms can occur as well. Symptoms of CIPN may lead to dose reduction or even early cessation of chemotherapy and therefore may affect tumor control and survival in cancer patients. Furthermore, CIPN impairs quality of life (QoL), functional capacity, and increases annual costs of health care.^[3]^ Several factors have been identified which affect the risk of developing CIPN like smoking, low creatinine clearance, preexisting neuropathy or genetic predisposition^[4]^; however, etiology and underlying mechanisms are still controversial.

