### Statistical analysis

3.19

Statistical analyses are elaborated in a prespecified statistical analysis plan. The primary endpoint is a change in the EORTC-QLQ-CIPN 20 score during the 8 weeks of intervention. For our primary endpoint, we will use an intention-to-treat analysis according to the CONSORT statement.^[19]^ Data that are missing at completely random (unrelated to any variable in the data set) or at random (related to some variable, but not to the outcome itself) will be imputed.^[25]^ If missing items in questionnaires exist, the patient's previous responses to the same item will be used.^[21]^ Further analyses will include a per-protocol analysis (primary and secondary outcomes) to test the consistency of intervention effects across important subgroups, for example, type of chemotherapy. Furthermore, we will analyze the intensity of intervention (compliance) and the effect on the primary endpoint (eg, comparison of infrequently and frequently use of device). A minimum use on 5 of 7 days per week is required. All tests are 2-tailed, and a 5% probability level is considered as significant. Statistical analyses are carried out after the end of the trial, with no interim analysis planned. All statistical analyses are performed with IBM SPSS Statistics 23.0.

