## Discussion

4

This pilot study aims to evaluate the efficacy of home-based HTEMS in CIPN and to determine the feasibility of a further large-scale RCT. To date, little research on high-tone therapy in CIPN has been carried out, even if this approach is widely used in clinical practice. We suppose that a structured treatment regime with high-tone therapy can improve patient care and symptom management of CIPN. Based on clinical observations, the effect of HTEMS on symptoms of CIPN seems promising. Although CIPN affects many patients with cancer, evidence for an effective therapy is still lacking. We cannot completely rule out that the therapy response in this pilot study is different depending on the type of chemotherapy administered. Oxaliplatin and paclitaxel can have different effects regarding the temporal course and localization of symptoms. Nevertheless, we decided to include different groups of patients. One reason is that there is no mandatory relation between the effect of HTEMS and the administered substance. CIPN causes predominantly sensory symptoms; motor or autonomic symptoms are much less common. Typically, oxaliplatin induces an acute sensory neurotoxicity with rapid onset of cold-induced distal dysesthesia and/or paraesthesia. The symptoms occur mostly during or shortly after administration and are transient and mild. With prolonged oxaliplatin treatment, a cumulative sensory peripheral neuropathy develops causing superficial and deep hypaesthesia and functional impairment. Furthermore, oxaliplatin affects hands more severely than feet.^[2]^ Neuropathy caused by taxanes develops cumulatively over time and typically improves after chemotherapy cessation. Oxaliplatin-related symptoms, in contrast, may get worse for several months after stopping chemotherapy, a phenomenon called “coasting-effect.”^[2]^ In this pilot study, we will include only patients with persisting CIPN 4 to 24 weeks after finishing the neurotoxic chemotherapy to exclude patients with spontaneous remission of sensory neuropathy.

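### Symptom aggravation stops treatment and is also the adverse direction of the primary endpoint, yet the text schedules no outcome assessment for patients who stop early and its imputation rule does not reach them

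*Protocol article*

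**What the plan says.** Section 3.13 (Potential harms and patient safety) states: "Stopping criteria comprise: dysesthesia, aggravation of symptoms, adverse events with the devices, incompatibility of the electrodes". The list goes on to disease progression and newly arising exclusion criteria. Aggravation has no grade, duration, comparison with baseline or causal qualifier, and the section does not say whether stopping means the device or study participation.

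Section 3.19 (Statistical analysis) makes the change in the CIPN20 score over the 8 weeks the primary endpoint and plans an intention-to-treat analysis. Data missing completely at random are to be imputed, as are data missing "at random (related to some variable, but not to the outcome itself) will be imputed". For missing questionnaire items, the patient's earlier answer to that item is used.

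The final assessment is timed in three places:
- Section 3.10 (Follow-up, final examinations): "After 8 weeks of electrotherapy (HTEMS or TENS), the outcome assessments (physician-reported outcome and patient-reported outcome) from baseline will be repeated".
- The Abstract's Methods paragraph likewise counts from completed home therapy.
- Section 3.15.2 (Clinician-reported outcome) puts the follow-up eight weeks after the intervention.

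For patients who do not complete the course, section 3.12 (Monitoring) records their number and reasons.

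On natural course, the Discussion says: "Oxaliplatin-related symptoms, in contrast, may get worse for several months after stopping chemotherapy". It says that taxane neuropathy typically improves once chemotherapy ends. Enrolment and start of therapy fall 4 to 24 weeks after chemotherapy (sections 3.2 and 3.7.1).

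**The concern.** Each rule is ordinary by itself; the difficulty lies in the combination. A patient whose neuropathy worsens is stopped because of that worsening, and the same worsening would have been a poor primary outcome. If the final assessment is then read as belonging to those who complete eight weeks of therapy, the poorest outcomes are the ones not recorded, and the imputation rule does not cover them because their absence is related to the outcome. The analysis would be called intention-to-treat but would in effect compare patients who did not worsen.

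Stopping need not be balanced. Participants are not blinded (section 3.6), so reports of aggravation could differ by arm. Spontaneous worsening is described for oxaliplatin and not for taxanes, so stopping could also differ by agent, which is the example subgroup in section 3.19. Section 3.18 expects the pilot to inform assumptions on effect size and variability for a later trial. Losing one tail of the outcome distribution would distort both.

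**Working it through.** **Does the text lead to the loss?**

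1. *Trigger.* Aggravation of symptoms (3.13) and a rise in the CIPN20 score (3.14.1 and 3.19, higher meaning worse) describe the same thing in the same direction. Stopping therefore depends on the outcome.
2. *Can it occur without the device?* Yes, for one agent. Oxaliplatin symptoms "may get worse for several months after stopping chemotherapy", and a window of 4 to 24 weeks overlaps a period of several months.
3. *Is there a visit after stopping?* None is stated. The Abstract and 3.10 count through eight weeks of therapy. Section 3.15.2, read literally, is eight weeks later than that. No statement is anchored to randomisation or start of therapy.
4. *Does imputation cover the gap?* Not by its own definition, since the stated rule stops at missingness unrelated to the outcome. The previous-answer rule concerns single items. If it were stretched to a whole missing form, the only earlier form is baseline.

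**How large would the effect be?** The article gives no effect size, SD, drop-out rate or stopping frequency, so there is no figure of the plan's to reproduce. All inputs below are assumptions.

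- Change score in SD units, positive meaning worse: TENS ~ N(0, 1), HTEMS ~ N(−0.5, 1). The true difference is −0.5.
- Every patient with a change above a threshold c stops and has no final score. c is the TENS 90th, 80th or 70th percentile and is the same in both arms.
- There are 25 patients per arm (50 randomised 1:1).

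Formulas, with φ and Φ the standard normal density and distribution function:
- TENS mean among those assessed: −φ(c)/Φ(c)
- HTEMS mean among those assessed: −0.5 − φ(c+0.5)/Φ(c+0.5)
- Patients lost: 25 × {[1 − Φ(c)] + [1 − Φ(c+0.5)]}

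| TENS stopping | c | TENS mean | HTEMS mean | Observed difference | Share of truth | HTEMS stopping | Lost of 50 |
|---|---|---|---|---|---|---|---|
| 10% | 1.282 | −0.1755/0.90 = −0.195 | −0.5 − 0.0816/0.9626 = −0.585 | −0.390 | 78% | 4% | 3.4 |
| 20% | 0.842 | −0.2800/0.80 = −0.350 | −0.5 − 0.1622/0.9101 = −0.678 | −0.328 | 66% | 9% | 7.2 |
| 30% | 0.524 | −0.3477/0.70 = −0.497 | −0.5 − 0.2361/0.8472 = −0.779 | −0.282 | 56% | 15% | 11.3 |

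**Would carrying baseline forward repair it?** Setting the change of stopped patients to 0 gives differences of −0.387, −0.337 and −0.312, so it does not.

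**Other assumed effects.** Simulation with cut-offs of 0.5 to 1.5 SD gives, among those assessed, −0.16 to −0.25 for a true −0.30, and −0.48 to −0.69 for a true −0.80.

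**Opposite direction.** Suppose there is no true difference but only HTEMS patients stop, the worst 10%, 20% or 30% of them. The assessed HTEMS mean is then −φ(c)/Φ(c), the TENS column above, against 0 in TENS. That is an apparent benefit of 0.195, 0.350 or 0.497 SD. This is an extreme case, shown only because it reverses the sign of the bias.

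**The case against.** **The article does not say that stopped patients go unassessed.** This is the strongest objection. Section 3.10 may be no more than a visit schedule. Intention-to-treat is planned alongside a separate per-protocol analysis, the comparison of frequent and infrequent device use needs outcomes from poor adherers, and section 3 gives the trial an 8-week observation time. The article is a condensed account and refers to an analysis plan that is not shown. This stands, and it makes the bias conditional. It does not remove the mismatch between a stopping rule that generates outcome-related missingness and an imputation rule that excludes it, nor the conflicting timing statements. Both are in the published text.

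**The magnitude assumes what it shows.** Effect size, threshold and total non-assessment are all supposed. This also stands: the table illustrates a consequence and predicts nothing about this trial.

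**A safety rule is not contradicted by the possibility of natural worsening.** This is fair. The list sits in the harms section, next to the study team's judgement on whether an event is associated with the intervention. Whether expected worsening should stop treatment is a clinical matter.

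**A stronger reading that fails.** A reader might infer that dysesthesia, the other criterion, is part of the enrolled condition, so that some patients would meet a stopping criterion at entry. The Discussion does say that "oxaliplatin induces an acute sensory neurotoxicity with rapid onset of cold-induced distal dysesthesia and/or paraesthesia", but its account of that acute form continues: "The symptoms occur mostly during or shortly after administration and are transient and mild". It describes the cumulative oxaliplatin form as hypaesthesia, and the Introduction's description of CIPN does not name dysesthesia: "It often presents with symptoms like paresthesia and numbness or tingling, but pain and motor symptoms can occur as well". Nor does the article say that platin patients in general are expected to worsen: it says that oxaliplatin symptoms may.

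**Conclusion.** The point holds for aggravation of symptoms. An unqualified, outcome-dependent stopping criterion meets a final assessment worded around completed therapy, inconsistent timing statements, and an imputation rule limited to missingness unrelated to the outcome. Followed literally, the plan can lose its worst outcomes from the intention-to-treat comparison and has no stated means of recovering them.

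The size is conditional on stopped patients not being assessed. With an assumed true effect of 0.5 SD and 10% to 30% of TENS patients stopping at a common threshold, the observed difference would be 0.39 to 0.28 SD, with about 3 to 11 of 50 patients lost. That scenario biases toward no difference. Device-caused aggravation under HTEMS could push the other way, so the direction cannot be assumed. The documents do not support a claim that patients will be removed in this way, or that dysesthesia at entry creates a contradiction. The change is worth making before analysis because it is cheap and closes the gap whichever way stopping falls.

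**What to change.** 1. Replace the timing statements in the Abstract, section 3.10 and section 3.15.2 with one anchor: 8 weeks from start of therapy, for every randomised patient, whether or not device use stopped.
2. State that stopping the device does not end outcome follow-up.
3. State in section 3.19 that these values enter the intention-to-treat analysis.
4. Separately, the clinical team should reconcile section 3.13 with the Discussion on worsening that may come from the disease course. No clinical rule is proposed here.

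The cost is protocol wording plus a final examination and questionnaires for the few patients who stop, at a visit already planned for the others. Some stopped patients may still decline that visit, so a smaller amount of missing data may remain.

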### Primary outcome

3.14

#### Patient-reported outcome

3.14.1

The EORTC QLQ-CIPN 20 contains 20 items assessing sensory (9 items), motor (8 items), and autonomic symptoms (3 items), using a 4-point Likert scale (1 = “not at all,” 2 = “a little,” 3 = “quite a bit,” and 4 = “very much”). All scale scores are linearly converted to a 0 to 100 scale (0 = no sensory impairment, 100 = worst sensory impairment).^[20]^

### Secondary outcomes

3.15

#### Patient-reported outcome

3.15.1

The EORTC QLQ-C30 questionnaire is an integrated system for assessing the QoL of cancer patients participating in clinical trials. All of the scales and single-item measures range in score from 0 to 100.^[21]^

#### Clinician-reported outcome

3.15.2

Baseline assessment is performed within 4 to 24 weeks after finishing the chemotherapy. Follow-up assessment is performed 8 weeks after intervention.

We use a standardized routine clinical test battery in our clinical examination containing the following assessment methods:

1.Vibration sensibility: evaluated by the use of a graduated Rydel-Seiffer tuning fork (128 Hz) with a scale from 0 to 8. Due to age-related neural deconditioning, values ≤4 are considered pathological for patients ≥60 years’ old, for patients <60 years’ old, scoring ≤5 is regarded as pathological.^[22,23]^2.Tendon reflex: Achilles tendon and patellar tendon reflex is assessed with a reflex hammer and graded on a 5-point scale of 0 to 4 with 0 being no response, 1+ being diminished/low normal, 2+ being average/normal, 3+ being brisker than average/possibly indicative of disease, and 4+ being very brisk, hyperactive, with clonus.^[24]^3.Temperature sensibility: Assessment by using TipTherm (tip therm GmbH, Düsseldorf, Germany). The examiner places the 2 circular end faces of the instrument alternately and in an irregular sequence on the back of the patient's foot and asks for the sensory impression: cold or less cold? Only correct answers suggest an intact temperature discrimination capability. Incorrect answers or uncertainties are to be understood as temperature sense—disturbance at the investigation site.4.Perception of touch: stroking patients’ upper legs, lower legs, and feet to detect reduced or altered sensation due to demyelination or axonal degeneration.^[22]^5.Strength of the lower muscles is assessed by asking the patient to perform toe standing/walking and heel standing/walking on both feet (possible, not possible)

### Outcome Assessment

3.16

For outcome assessors, the treatment allocation remains blinded. The QoL disease-specific CIPN20 questionnaire and EORTC QLQ-C30 questionnaire are provided in the patient's language.

### Data management

3.17

Baseline and follow-up data will be recorded pseudonymized using a CRF. Forms will be checked all for completeness and plausibility. In case of missing or implausible data, the responsible outcome assessor will be contacted.

### Sample size

3.18

Since this is a pilot trial, a formal sample size calculation was not performed. We aimed to recruit 50 patients as that was the sample size that we estimated would be feasible within this pilot project to provide sufficient scientific validation. Pilot studies are important to be confident that the intervention can be delivered as intended. It will also allow better assumptions about effect sizes and variability.

### Statistical analysis

3.19

Statistical analyses are elaborated in a prespecified statistical analysis plan. The primary endpoint is a change in the EORTC-QLQ-CIPN 20 score during the 8 weeks of intervention. For our primary endpoint, we will use an intention-to-treat analysis according to the CONSORT statement.^[19]^ Data that are missing at completely random (unrelated to any variable in the data set) or at random (related to some variable, but not to the outcome itself) will be imputed.^[25]^ If missing items in questionnaires exist, the patient's previous responses to the same item will be used.^[21]^ Further analyses will include a per-protocol analysis (primary and secondary outcomes) to test the consistency of intervention effects across important subgroups, for example, type of chemotherapy. Furthermore, we will analyze the intensity of intervention (compliance) and the effect on the primary endpoint (eg, comparison of infrequently and frequently use of device). A minimum use on 5 of 7 days per week is required. All tests are 2-tailed, and a 5% probability level is considered as significant. Statistical analyses are carried out after the end of the trial, with no interim analysis planned. All statistical analyses are performed with IBM SPSS Statistics 23.0.

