**Methods::**

This pilot study aims to investigate whether the application of home-based high-tone external muscle stimulation therapy (HTEMS) improves symptoms of CIPN. The trial is planned as a therapist- and assessor-blinded, 1:1 randomized controlled study. A total of 50 patients with chemotherapy-induced peripheral polyneuropathy will be included. All patients will perform therapy at home. Study participants will be allocated randomly to the HTEMS therapy (intervention group) or to the transcutaneous electrical nerve stimulation (TENS, control group), respectively, following a standardized therapy schedule. Compliance of participants can be verified by reading out the tool box. Outcomes will be evaluated at baseline and after 8 weeks of home-based therapy. The primary outcome includes improvement of CIPN according to the patient-reported EORTC QLQ-CIPN 20 questionnaire. Secondary outcomes are the patient-reported change in health-related quality of life and clinician-reported changes of vibration sensibility, tendon reflexes, temperature sensibility, perception of touch, and strength of the lower leg muscles. Further a safety- and process evaluation will be performed.

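### Filling a missing questionnaire item with the patient's previous answer puts zero change for that item into the primary change score, and cannot fill an item missing at baseline

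*Protocol article*

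**What the plan says.** Section 3.19 (Statistical analysis) defines the outcome: "The primary endpoint is a change in the EORTC-QLQ-CIPN 20 score during the 8 weeks of intervention". It promises imputation of data missing completely at random or at random, without naming a method there. It then sets a rule for individual missing questionnaire items: the patient's "previous responses to the same item will be used".

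The schedule has two questionnaire time points. The abstract states: "Outcomes will be evaluated at baseline and after 8 weeks of home-based therapy". Section 3.9 (Baseline-examination) covers the first: "Participants are asked to fill out the questionnaires (QLQ-CIPN 20 and QLQ 30) in paper form". Section 3.10 (Follow-up, final examinations) covers the second, at 8 weeks, when "the outcome assessments (physician-reported outcome and patient-reported outcome) from baseline will be repeated". The only contact between them has another purpose: "Patients will be contacted by the study team after 1 week to identify any problems with the device".

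Section 3.14.1 describes the instrument as 20 items (9 sensory, 8 motor, 3 autonomic), each answered from 1 to 4, and adds: "All scale scores are linearly converted to a 0 to 100 scale".

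**The concern.** With two time points, the only previous answer to a week-8 item is the baseline answer. Copying it forward fixes that item's change at zero, whatever happened to the patient, and the filled value enters the analysis as though the patient had given it. True change in either direction is pulled toward zero, and the uncertainty of the filled values is ignored.

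Zero change is not a neutral guess in this population. The Discussion expects taxane neuropathy typically to improve after chemotherapy ends, and oxaliplatin symptoms possibly to worsen for months. Participants know which device they use (section 3.6), so unequal item non-response between arms is possible, and the error need not then cancel in the comparison.

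The rule also has a gap. A blank item at baseline has no earlier answer, so half of the change score has no workable item rule.

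This matters even in a pilot. Section 3.18 wants the trial to inform later assumptions about effect size and variability, and the rule distorts both.

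**Working it through.** The article gives no effect size, standard deviation or item-missing rate, so it has no figure to reproduce. The check is arithmetic on the scoring described in section 3.14.1.

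**Inputs from the article.** Items scored 1 to 4; linear conversion to 0–100; K = 20 items overall or K = 9 for the sensory scale; questionnaires at baseline and week 8 only.

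**Formula.** Score = (item mean − 1)/3 × 100. If m of K items are blank at week 8 and take their baseline answers, those m items contribute 0. If the true change is the same on every item (an assumption), then

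recorded change = true change × (1 − m/K).

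**Share of the true change that is kept**

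| Items filled (m) | K = 20 | K = 9 |
|---|---|---|
| 1 | 19/20 = 95% | 8/9 = 89% |
| 2 | 18/20 = 90% | 7/9 = 78% |
| 3 | 17/20 = 85% | 6/9 = 67% |

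Both columns are shown because section 3.19 names the QLQ-CIPN 20 score without naming a subscale, while the 0 and 100 anchors in section 3.14.1 speak of sensory impairment.

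**Direct check.** Let every item improve from 3 to 2. The true change is −33.33 points. On 20 items, 1 filled item gives −31.67 and 2 give −30.00. On 9 items, 1 filled item gives −29.63 and 2 give −25.93. These match the formula.

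**Between arms, no true difference.** Assume a true change of 15 points in both arms, with item-missing fractions f1 and f2. The false difference is 15 × (1 − f1) − 15 × (1 − f2) = 15 × (f2 − f1).

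| Missing, arm 1 against arm 2 | False difference (points) |
|---|---|
| 2% against 5% | 15 × 0.03 = 0.45 |
| 5% against 10% | 15 × 0.05 = 0.75 |
| 10% against 25% | 15 × 0.15 = 2.25 |

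**Between arms, a true difference.** Assume true changes of −15 and −5, a difference of −10.

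- Equal missingness of 5%, 10% or 20% gives −9.5, −9.0 or −8.0.
- If the arm with the larger change has 20% missing and the other 5%: −15 × 0.80 + 5 × 0.95 = −7.25.
- With those rates reversed: −15 × 0.95 + 5 × 0.80 = −10.25.

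So the rule usually dilutes an effect but can also enlarge one. All missing rates and true changes here are assumptions.

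**The case against.** Several points on the other side are fair.

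**Few items may be blank.** Inclusion requires the ability to complete questionnaires with or without help (section 3.2), assessment takes place at the institute (section 3.4), and forms are checked for completeness (sections 3.12 and 3.17). This stands as an argument about size. It lowers the number of filled items but does not change what the rule does to each one. A 25% rate would mean 5 of 20 items blank on average, which is the high end of the range shown.

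**The usual alternative also errs.** Averaging the items answered at the same visit assumes items of similar level. Take 9 sensory items, two at 4 and seven at 1, with no true change. The baseline score is (15/9 − 1)/3 × 100 = 22.2. If one of the items at 4 is blank at week 8, averaging gives (11/8 − 1)/3 × 100 = 12.5, a false improvement of 9.7 points. Here the previous-response rule gives the correct 0. This stands and shapes the fix.

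**The unseen statistical analysis plan may say more.** It may, but section 3.19 itself states the rule. The point concerns a rule that has been set, not detail left out.

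**Stronger readings.** A reader might infer that the rule sets the whole endpoint to zero, or that it scores every dropout as unchanged. The text supports neither. The zero applies per filled item and reaches the whole scale only if every item is blank, and the wording covers missing items without saying that it covers a wholly missing questionnaire. Nor does the item rule contradict the imputation sentence before it: a general rule and a specific one can coexist.

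**Conclusion.** The point holds at item level. With this schedule, a missing week-8 item takes its baseline answer and adds nothing to the primary change score, and a missing baseline item cannot be filled. Under equal change on all items, each filled item costs 5% of the true change on a 20-item score and 11% on the sensory scale. False differences between arms run from 0.45 to 2.25 points over the assumed range.

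The actual size is unknown, because the article gives no item-missing rate, and it is probably small if few items are blank. Without a standard deviation, it cannot be shown that even 2.25 points would alter a conclusion with 50 patients. The case for change rests on a predictable error in the primary endpoint that is cheap to remove.

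**What to change.** Replace the previous-response rule in the primary analysis, in section 3.19 and in the statistical analysis plan, with one of these:

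1. Score each scale from the items answered at the same visit when at least half are present.
2. Preferably, because items may differ in level, multiply impute missing items at either visit from the same-visit items, the other visit's answer to that item and the treatment arm. Two visits of 20 items make 40 item variables for 50 patients, so restrict the predictors to the scale concerned.

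Handle scales with fewer than half their items, and wholly missing questionnaires, by one named multiple-imputation method. The article names no method, so this is a proposal. Either option also deals with items missing at baseline. Keep the previous-response rule only as a sensitivity analysis, and report the number of missing items by arm and visit.

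The cost is a few sentences and a little more analysis work, with no extra data. The drawback of option 1 is its assumption that the items of a scale are of similar level.
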